### Randomization and Blinding

The study participants will be recruited from 10 preidentified study sites in the Pathanamthitta district of Kerala. Recruitment will be achieved according to the study inclusion criteria and based on the initial and final screening. The participants will be allocated to either intervention or placebo groups as per the randomization sequence generated using PASS 2021 (v21.03) software. Prenumbered or coded identical containers will be used for allocation concealment. The PI at CCRH headquarters will be involved in the sequence generation process and allocation concealment procedure. The PI will label the interventions as per the randomization codes, which will be handed over to the site PIs. The site PIs will enroll participants and randomly assign participants to interventions. The trial participants and the site PIs assigning participants to interventions will be blinded. To ensure blinding quality, the packaging for both the intervention and placebo will be identical in shape, color, size, taste, and odor. The unblinding will be done only at the end of the study by the PI at CCRH headquarters. If the participants reported severe adverse events (SAEs) during the trial, unblinding may be performed per Data and Safety Monitoring Board (DSMB) or ethical committee recommendations. The reason for urgent unblinding should be well-documented.

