### Dropout, Withdrawal, and Suspension Criteria

#### Dropout Criteria

Participants who develop SAEs will be withdrawn from the RCT after reporting to the Institutional Ethics Committee. Participants who develop concomitant diseases of viral origin during the trial that would affect the efficacy and safety assessment intervention, participants with poor compliance, those changing the intervention or adding therapy prohibited under the study for any reason, breaking the double-blind setting of the clinical trial, and those found to have any serious violations of the inclusion/exclusion criteria after enrollment will be withdrawn from the study.

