#### Conditions for Trial Suspension

If any SAE occurs during the study, the trial will be terminated immediately as per recommendations of the DSMB and Ethics Committee. If there is a major error in the trial or a serious protocol deviation during implementation, which would make it difficult to evaluate the drug efficacy and safety, the trial will be stopped. The trial will also be terminated if the funding agency or collaborating institution requests to stop the trial or if the regulatory authority cancels the trial. The Council is entitled to terminate the trial prematurely at any time for medical and/or organizational reasons. This decision will generally be made based on the recommendations of the Scientific Advisory Board, CCRH, New Delhi, or the Director of Homoeopathy, Government of Kerala.

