#### Criteria for Discontinuing or Modifying Allocated Interventions

All participants shall be advised to telephonically inform the site PI if they develop symptoms similar to COVID-19 infection. If any participant reports symptoms, the intervention shall be stopped, and if testing positive for COVID-19 in RT-PCR, the local health authorities will be informed by the site PI. Study participants shall be advised to take the treatment of their choice from the dispensary at the study site through teleconsultation or from other medical facilities nearby. In case of requirement, the study participants will also be provided support through an already allocated medical health insurance policy (valid for 1 year) for their hospitalizations or other related treatments. They shall be under observation in this study until their recovery from the symptoms and may report any events that may be an SAE. The site PI will record the days to recovery, disease stage, and severity of symptoms, among other clinical data. The details of treatment and progress will be acquired from family members or the participants themselves, which may be recorded in the follow-up and participant study forms in the CRF. A COVID-19–positive status with the intervention or placebo will be considered as the study endpoint for participants with a positive test result on RT-PCR.

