#### Strategies to Improve Adherence to Intervention Protocols and Procedures for Monitoring Adherence

The participants must visit the study site for the 3 days of the intervention at each schedule. To ensure compliance, the independent dispenser will only administer the medicine and placebo to the participants at the prescribed dosage. The intervention procedure will be under the supervision of the site PI to ensure adherence. Any deviation in these procedures will be recorded in the Deviation/Unanticipated Problem Tracking Log of the CRF. Participants will be under observation of the site PI at the study site for at least 1 hour to monitor for any immediate drug-related adverse effects, which will be recorded and informed to the PI. If the participant feels any discomfort, they will be medically examined by the site PI. Vital parameters such as heart rate, respiratory rate, and blood pressure will be monitored and recorded. In case of any SAE, the participant will be referred to a tertiary-care facility after receiving appropriate first aid at the site by the site PI. The DSMB and Ethics Committee will be duly informed about these events. Blood samples will be drawn and stored 1 day before and after 3 days of the intervention and on the last day of the study by the designated laboratory involved in sample collection and storage. During each visit, participants will be compensated for travel from their home to the study site and provided with protein-based refreshments to minimize their difficulty at each visit to the study site, thereby improving adherence.

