### Adverse Events

Any SAE that occurs during and after the study period and is possibly considered due to the study intervention or participation will be recorded and reported immediately to the concerned ethical committee and DSMB.

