## Abbreviations

AA30CH: Arsenicum album 30CH
CBC: complete blood count
CCRH: Central Council for Research in Homoeopathy
CRF: case record form
CTRI: Clinical Trials Registry-India
DBT-THSTI: Department of Biotechnology, Translational Health Science and Technology Institute
DC: dendritic cell
DSMB: Data and Safety Monitoring Board
IFN: interferon
IL-1R: interleukin 1 receptor
LFT: liver function test
NCDC: National Centre for Disease Control
NHRIMH: National Homoeopathy Research Institute in Mental Health
NK: natural killer
PBMC: peripheral blood mononuclear cell
PI: principal investigator
RCT: randomized controlled trial
RFT: renal function test
RT-PCR: reverse transcription-polymerase chain reaction
SAE: severe adverse event
SPIRIT: Standard Protocol Items: Recommendations for Interventional Trials
TLR: Toll-like receptor
TPR: test positivity rate
WHO: World Health Organization

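### SAE is spelled out as *severe* adverse event, and that label triggers reporting, referral, withdrawal, possible unblinding and possible termination

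*Protocol article*

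**What the plan says.** The protocol article spells out SAE twice. Randomization and Blinding has "If the participants reported severe adverse events (SAEs) during the trial, unblinding may be performed" and makes this depend on a recommendation from the DSMB or the ethics committee. The Abbreviations list has "SAE: severe adverse event".

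The label is then used in these rules:

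- Dropout Criteria: "Participants who develop SAEs will be withdrawn from the RCT after reporting to the Institutional Ethics Committee".
- Conditions for Trial Suspension has this rule: "If any SAE occurs during the study, the trial will be terminated immediately as per recommendations of the DSMB and Ethics Committee".
- Strategies to Improve Adherence: "In case of any SAE, the participant will be referred to a tertiary-care facility". The same section says that the DSMB and Ethics Committee are informed.
- Adverse Events: "Any SAE that occurs during and after the study period and is possibly considered due to the study intervention or participation" is what must be reported at once to the ethics committee and the DSMB.
- Criteria for Discontinuing or Modifying Allocated Interventions: participants with COVID-19-like symptoms are observed until recovery and "may report any events that may be an SAE". This section also foresees hospital stays, for which insurance cover is arranged.

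Research Ethics Approval commits the trial to Good Clinical Practice standards.

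**The concern.** Severity and seriousness are different properties. Severity grades how intense an event is. Seriousness depends on its consequence, such as a hospital admission. An expedited safety route is meant to be driven by consequence. Here the label that opens the route names intensity.

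Taken at its word, the label errs in both directions. A participant admitted to hospital with an illness of moderate intensity has no SAE. A participant with a short, intense episode that needs no care has one, and the withdrawal and referral rules then apply to that participant. At stake is which clinical events reach the two oversight bodies promptly. Their discretion over unblinding and termination can act only on events that have been sent to them.

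**Working it through.** No arithmetic applies, because the point rests on no rate, effect size or sample size. The check was to trace each use of SAE, *severe* and *serious* in the article and match it to the action it triggers.

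**Step 1: the term.** SAE is expanded in two places, and both (2 of 2) read *severe*. None reads *serious*. The authors do use *serious*, but only for violations of the eligibility criteria (Dropout Criteria) and for a protocol deviation (Conditions for Trial Suspension). A repeat in text and list is more than a single typing slip.

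**Step 2: what the label triggers.**

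| Section | Action | Further condition stated |
|---|---|---|
| Adverse Events | Immediate report to ethics committee and DSMB | Possible relation to intervention or participation |
| Strategies to Improve Adherence | Tertiary referral; DSMB and Ethics Committee informed | None |
| Dropout Criteria | Withdrawal after report to the Institutional Ethics Committee | None |
| Randomization and Blinding | Unblinding | Permissive; DSMB or ethics committee recommendation |
| Conditions for Trial Suspension | Termination | DSMB and Ethics Committee recommendation |

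**Step 3: what does not use the label.** Four safety actions run without it:

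- recording any prompt reaction to the drug and examining any discomfort (Strategies to Improve Adherence);
- stopping the intervention when COVID-19-like symptoms are reported (Criteria for Discontinuing or Modifying Allocated Interventions);
- reporting other medical problems to the PI (Relevant Concomitant Care);
- laboratory safety review by the DSMB after each of the three schedules (Data Monitoring and Management).

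**Step 4: do those routes close the gap?** Take a participant hospitalised with an illness of moderate intensity that is possibly related to participation. Under Relevant Concomitant Care the event is documented and reaches the PI, but that section has no rule sending it on to the DSMB or ethics committee. The review after each schedule carries laboratory parameters, not clinical events. Interim reports also go to the DSMB (Assessment, Data Analysis, and Manuscript Preparation), but their content is not stated and they are not immediate. If the event is not called an SAE, nothing in the article sends it promptly to either body.

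**Step 5: the relatedness condition.** A hospitalisation judged unrelated stays outside the Adverse Events rule whichever word is used. The notice rule under Strategies to Improve Adherence and the report before withdrawal under Dropout Criteria state no such condition. The scope of reporting therefore differs between sections, apart from the question of the term.

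**The case against.** The strongest reply is that this is a wording slip for *serious*. Prompt reporting to two oversight bodies and tertiary referral fit a seriousness concept. The article invokes Good Clinical Practice, and Pretrial Preparation refers to detailed operating procedures and case record forms that are not shown. Sites may well apply outcome-based criteria. A hospitalised participant is also not lost from view: medical problems reach the PI, and symptomatic participants are followed to recovery with the severity of their symptoms recorded.

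Much of this stands. The article only expands an abbreviation, and the lack of seriousness criteria or an intensity scale may be condensation, so that absence is not a finding. A reader might infer that the sites will each set their own threshold. With the procedures unseen, that is a risk and not an established fact.

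A reader might also infer that all safety handling depends on the label. The four actions in Step 3 of the working show that it does not. Nor does the label alone decide unblinding or termination, which pass through committee recommendations. Finally, a reader might conclude that the safety results are undermined because SAE counts would be unreliable. SAE counts are not a listed outcome: the toxicity evaluation is restricted to hepatic, renal and haematological measures.

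What the reply does not remove is the stated term. If the unseen procedures use outcome-based criteria, the published text conflicts with them and still needs correcting.

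**Conclusion.** The point holds as an error in a stated, operative term. Both expansions of SAE name intensity, and the label governs immediate reporting, referral with notice to the oversight bodies, withdrawal, possible unblinding and possible termination. Read literally, a hospitalisation of moderate intensity falls outside the prompt route to the DSMB and ethics committee, which sits badly with the Good Clinical Practice commitment. An intense but harmless event falls inside it.

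The number of events affected cannot be derived from the article, since no event rate or grading is given. The conclusion assumes that sites follow the article's wording. If their procedures already use seriousness, what remains is an inconsistency between documents. The correction should be made, but it does not call into question the listed outcomes or the safety handling that runs without the label.

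**What to change.** 1. In Randomization and Blinding and in Abbreviations, replace the expansion with *serious adverse event*, in the Good Clinical Practice sense to which Research Ethics Approval commits the trial. Use it for classification and reporting.
2. If intensity is collected, record it as a separate item.
3. Reconcile Dropout Criteria, Conditions for Trial Suspension, Criteria for Discontinuing or Modifying Allocated Interventions, Strategies to Improve Adherence, and Adverse Events with the corrected term. State whether the relatedness condition in Adverse Events is meant to apply to the other reporting rules.
4. What should lead to withdrawal, referral, unblinding or termination remains for the sponsor to set; no rule is proposed here.

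The cost is small but not nil. Somewhat more events will be reported. The withdrawal and termination wording must be rechecked, because under the corrected term those rules would cover a different set of events. The case record forms are already printed, and Protocol Amendments requires ethics approval and a written justification. Enrolment was complete by April 3, 2023, so the benefit lies in classifying events already recorded and in handling those still to be reported; the Adverse Events rule extends beyond the study period.

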### Pretrial Preparation

The selection of 10 homeopathic dispensaries was based on the COVID-19 incidences and TPR in the Pathanamthitta district. The CCRH conducted a preliminary short survey to identify these 10 sites. Following Central Ethics Committee approval, the clinical trial was registered in the Clinical Trials Registry-India (CTRI) under registration number CTRI/2022/08/045089 (August 30, 2022). An Indian Council of Medical Research–approved and National Accreditation Board for Testing and Calibration Laboratories–accredited laboratory was engaged for RT-PCR screening, hematology, clinical biochemistry, and peripheral blood mononuclear cells (PBMCs) isolation. The isolated PBMC samples for conducting immunological assays will be stored in a –80°C freezer located at the central laboratory facility in the facilitating institute of the RCT. The isolated PBMC samples will be transported to the DBT-THSTI in batches for the immunological assays. The blood samples collected from the study participants will also be used to evaluate the safety profile of the drug, mainly in terms of hematology parameters, liver function, and renal function. Training will be administered to the laboratory staff for the procedures of PBMC isolation. A mock drill will also be conducted at one of the study sites to identify the practical difficulties encountered during the screening, participant recruitment, sample collection, and storage procedures (no participant recruitment will be allowed with the mock drill). All site PIs in the 10 sites will be included in the mock drill for the practical demonstration of handling the samples and to streamline the logistics involved in the sample transportation and PBMC isolation procedures until storage in the –80°C freezer. Detailed standard operating procedures for the procedures and data collection, case record forms (CRFs), and screening forms were designed and printed as individual booklets.

### Screening and Enrollment

All the participants will be voluntarily invited to the study and then required to sign an informed consent form containing information on the regulatory authorities and related procedures, including initial RT-PCR screening, laboratory screening, and subsequent randomization after enrollment. The RT-PCR test will screen the participants fulfilling the eligibility criteria for an ongoing COVID-19 infection. If the RT-PCR test result is found to be negative for COVID-19, the participant will be investigated for an initial (baseline) LFT, RFT, CBC, and peripheral blood smear as part of the second screening for any abnormal parameters. Those with borderline elevated or normal values will be enrolled in the trial, followed by randomization. Screened participants with positive RT-PCR reports for COVID-19 will be notified to the local health authorities. Their health status will be telephonically monitored during quarantine or hospital stay by the site PI. Each study site will maintain a log register that records all details of the screened participants and the reason(s) for exclusion. Enrolled participants will then be randomized and allocated to the intervention or the placebo arm as per the generated randomization sequence using PASS software version 21.03.

### Assessment, Data Analysis, and Manuscript Preparation

The laboratory parameters recorded during the seven blood draws of each participant will be analyzed for any statistically significant changes using appropriate statistical tests. The PBMCs isolated during the seven blood draws and stored in the –80°C freezer will be transported as air freight in liquid nitrogen tankers to DBT-THSTI, Faridabad, for immunological assays and data analysis. The interim reports will be confidentially submitted to the designated DSMB, internal committees of CCRH, and Ministry of Ayush, Government of India, on availability as per requirements. Manuscripts with the study findings will be prepared and submitted to Scopus-indexed peer-reviewed journals. Patents pertaining to this RCT will be filed as per the directions of the Ministry of Ayush, Government of India.

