### Sample Size

The study is aimed at evaluating the immunologic responses of AA30CH. The study is based on earlier encouraging leads provided through community studies on the role of AA30CH in preventing COVID-19. Several parameters are in consideration for the evaluation of immunogenic responses. With regard to the computation of sample size, based on the literature and expert opinions, it is proposed to consider some limited immunologic parameters that are more relevant. Owing to the scarce availability of literature, it would be quite challenging to hypothesize the assumption. Assuming a type 1 error of 5% and a power of 80%, it was estimated that there would be 93 participants each in the intervention and control groups, with a total of 186 participants. This could be escalated based on attrition due to loss in follow-up. If this loss to follow-up is considered at 20%, a total of 112 participants have to be enrolled in each group, with a total sample of 224 that would need to be recruited for the study.

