### Statistical Analysis

Data analysis will be performed following the intention-to-treat/per-protocol method. The safety and immunological parameters will be analyzed at each of the seven time points and comparisons will be made between the subjects and groups. Additional analyses (eg, subgroup analyses according to age, sex, and perceived risk categories) will also be performed based on the evolving trends from the analysis. A trial statistician will be engaged for the statistical analysis of the clinical trial.

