As mainly overseeing the primary objective of immunological efficacy and safety of AA30CH, this study also aims to assess the safety of AA30CH in terms of the results of LFTs, RFTs, CBCs, and peripheral smears between the intervention and placebo groups. Previously, the acute and subacute toxicity of AA30CH were investigated in an animal model and no adverse events or organ-related toxic effects were reported [46]. This study would also evaluate these findings in an RCT, which may support establishing the safety profile of AA30CH that could further open new vistas of research for an effective prophylactic therapy against SARS-CoV2 infection.

The timely, detailed investigation of the immunopharmacology of drug candidates is challenging [47,48]. In searching for therapeutic strategies against the COVID-19 pandemic, these essential investigations may be limited to a preliminary analysis or primary data obtained due to the pressing priority. Based on the objectives, our study is limited to the immunological responses of AA30CH against COVID-19 in healthy individuals; however, when AA30CH is mass distributed in an ongoing COVID-19 transmissible zone, a detailed investigation on the prevalence of COVID-19 incidence may provide more insights into its prophylactic efficacy.

In conclusion, the current RCT primarily emphasizes the immunological efficacy of AA30CH as a COVID-19 prophylaxis. Secondarily, the hematologic, hepatic, and renal toxicity evaluation of AA30CH would provide a comprehensive understanding of its use in healthy individuals; however, further directions on these parameters in comorbid conditions still need investigation.

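### Statistical significance is the only stated analysis criterion for laboratory toxicity; at about 90 per arm it says little about a 2-3% harm, and it also invites chance findings

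*Protocol article*

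**What the plan says.** Toxicity, measured by liver and renal function tests, blood count and peripheral smear, is a secondary outcome (Outcome Measures). Bloods are drawn on days 1, 5, 23, 27, 45, 49 and 66.

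On how these data are judged, Assessment, Data Analysis, and Manuscript Preparation says: "The laboratory parameters recorded during the seven blood draws of each participant will be analyzed for any statistically significant changes using appropriate statistical tests". Statistical Analysis says: "The safety and immunological parameters will be analyzed at each of the seven time points and comparisons will be made between the subjects and groups".

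The Discussion attaches two expectations to the result. One is that the trial will evaluate findings "which may support establishing the safety profile of AA30CH". The other is that "the hematologic, hepatic, and renal toxicity evaluation of AA30CH would provide a comprehensive understanding of its use in healthy individuals".

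Sample Size describes the calculation in terms of immunologic parameters and mentions no safety consideration. It gives no effect size, standard deviation or event rate, and says: "Owing to the scarce availability of literature, it would be quite challenging to hypothesize the assumption".

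Two further provisions bear on safety. Data Monitoring and Management sends the laboratory safety data to the DSMB after each schedule. Adverse Events requires SAEs to be reported to the DSMB and the ethics committee.

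**The concern.** A significance search answers whether a difference was detected. It does not answer how large a harm the data exclude, and a safety statement needs the second answer. If a product affects a small fraction of users, a between-arm test at this sample size will often be non-significant whether or not that harm exists. A non-significant result then gives little support for the Discussion's expectations.

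The criterion also fails the other way. It looks for any significant change, across several analytes and seven draws, and the article states no adjustment. Isolated significant results are therefore expected by chance, and the stated criterion gives no means of telling them from real signals.

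The Discussion reports that the product was distributed to millions of people as a preventive. What this trial can and cannot exclude should therefore be stated exactly.

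**Working it through.** **Inputs from the protocol article (Sample Size).** "Assuming a type 1 error of 5% and a power of 80%, it was estimated that there would be 93 participants each"; "If this loss to follow-up is considered at 20%, a total of 112 participants have to be enrolled in each group". The sidedness of the 5% level is not stated; two-sided is assumed below.

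**The plan's own figures.** 93 × 1.2 = 111.6, which rounds up to 112. Taking 20% off 112 leaves 112 × 0.8 = 89.6, about 90 evaluable per arm. The 93 cannot be reproduced because no effect size is given; solved backwards for a comparison of two means, it corresponds to a standardised difference of 0.411 (two-sided). No power or precision figure is given for safety.

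**Assumed inputs, not in the documents.** Background abnormality rates of 0%, 1%, 2% and 5%; an excess in the AA30CH arm of 2%, 3% or 5%; for continuous data, a shift of 3 or 5 SD in the affected fraction.

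**Check 1: counts of abnormal values.** Power is the sum, over all pairs (i, j) in which the AA30CH arm is significantly worse, of Bin(i; n, p0 + excess) × Bin(j; n, p0). Each cell gives Fisher / uncorrected chi-square power for one comparison.

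| n per arm | Background | Excess 2% | Excess 3% | Excess 5% |
|---|---|---|---|---|
| 90 | 0% | 1% / 11% | 5% / 29% | 30% / 66% |
| 90 | 1% | 2% / 12% | 7% / 23% | 26% / 45% |
| 90 | 2% | 3% / 10% | 8% / 17% | 22% / 34% |
| 90 | 5% | 4% / 7% | 7% / 12% | 17% / 24% |
| 112 | 0% | 3% / 19% | 12% / 43% | 49% / 82% |
| 112 | 1% | 5% / 16% | 13% / 28% | 38% / 54% |
| 112 | 2% | 6% / 12% | 12% / 21% | 32% / 43% |
| 112 | 5% | 5% / 9% | 10% / 15% | 22% / 30% |

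At a 2-3% excess no cell exceeds 29% at n = 90 or 43% at n = 112. At 5%, Fisher stays below one half throughout. Chi-square exceeds one half with zero background at either size, and with 1% background at n = 112.

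**Check 2: comparison of means.** Simulated two-sided t-test at n = 90, SD 1, with a fraction of the AA30CH arm shifted. By 3 SD it misses about 93% (2% affected), 92% (3%) and 86% (5%). By 5 SD in 5% it misses about 76%. A uniform shift of 0.5 SD is missed only 8% of the time, so the size is adequate for a general shift and inadequate for a rise confined to a few people.

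**Check 3: what zero events would exclude.** The two-sided 95% upper limit for 0/n is 1 − 0.025^(1/n). For n = 90 this is 4.0%; for n = 112 it is 3.2%.

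**Check 4: an illustration.** Five abnormal participants of 90 on AA30CH and none of 90 on placebo give Fisher p = 0.059, which is not significant. The exact 95% interval for the AA30CH rate is 1.8% to 12.5%. The interval shows what the p-value leaves out.

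**Check 5: chance positives.** With one analyte from each of the three panels at the six draws after day 1, there are 3 × 6 = 18 tests. If they were independent, the chance of at least one p < 0.05 under no effect is 1 − 0.95^18 = 60%. Correlation lowers this and more analytes raise it.

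**The case against.** The strongest objection is that this is a condensed article. Abnormality thresholds, shift tables and interval methods usually sit in a statistical analysis plan, which is not shown, and the choice of test is left open. That stands: the lack of such detail is no fault. The point rests on what the text does fix, namely significance as the criterion, set beside the safety expectations in the Discussion.

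Three stronger readings are tempting, and the documents do not support them.

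- **That a null result will be read as proof of safety.** No section says so. The first Discussion statement is hedged with may support, and the second goes on to say that comorbid conditions still need investigation. The mismatch is between the criterion and the hoped-for conclusion, not a declared rule.
- **That significance is the only way safety is judged.** The DSMB sees the laboratory data after each schedule, SAEs are reported, and participants are observed for at least 1 hour at the site. Large rises in a few people could be noticed there. These provisions protect participants, but they do not say how the between-arm outcome will be analysed or concluded.
- **That a toxicity of 2-5% would usually be missed and a wholly null result is likely.** At 5% this depends on the test and the background rate, as the table shows. The miss rates are for one comparison; over many analytes and draws, some significant result is quite likely by chance.

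It is also fair that a 3-SD laboratory rise is not in itself shown to be clinical harm.

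**Conclusion.** The point holds in a limited form. Significance is the only analysis criterion stated for laboratory toxicity, and it is poor in both directions: a single comparison has at most 29% power for a 2-3% excess with 90 per arm, or 43% with 112, while unadjusted repetition over analytes and draws yields chance positives. At a 5% excess the conclusion is mixed: missed more often than not by Fisher's test, and by a comparison of means at the shifts tried (3 and 5 SD), but not by an uncorrected chi-square with zero background.

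The excess rates, background rates and shifts are assumptions, as is two-sided testing. The upper limits of 3.2% to 4.0% for zero events rest only on the sample size. The point should be acted on, but it does not affect the primary immunological outcome.

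**What to change.** In Assessment, Data Analysis, and Manuscript Preparation and in Statistical Analysis, replace the significance criterion for the safety laboratories. For each liver, renal and blood-count analyte:

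- report by randomised arm the number of participants whose worst value after day 1 crosses a laboratory reference threshold fixed before unblinding;
- show the shift from day 1, because Screening and Enrollment admits borderline elevated values;
- give the AA30CH rate and the between-arm difference, each with a 95% confidence interval;
- state that absence of a significant difference will not be taken as evidence of safety.

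In the Discussion, limit the safety statement to the abnormality rate that the upper bound excludes, which is about 3-4% at best, with zero events.

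The cost is small. Enrollment is complete, and the change uses only data from the seven planned draws, with no new participants or procedures. The price is one more set of tables and a more modest safety claim.
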